| Visit Window            |                                       | - 6h    |   | ±1.5m  | ±3 m  | ±6 m | ±12 m | ±18 m | ±24 m | ±2 h | -2.5 h | -30 m |   | -30 m  |   | ±1.5 m | ±3 m  | ±6 m | ±12 m | ±18 m | ±24 m | ±2 h     | - 2.5 h | - 30 m |                                                 |  |  |

- f. [REDACTED]
- g. [REDACTED]
- h. [REDACTED]
- i. **Archival Tumor Tissue:** Archived FFPE specimen from a recurrent tumor or distant metastasis other than to bone will be required and collected for all participants. If the archived FFPE specimen is not available or sufficient, a fresh biopsy (before C1D1 treatment) will be mandatory. Additional information can be found in [Section 8.8.1](#) and the Laboratory Manual.
- j. [REDACTED]
- k. **Pfizer Prep D1 Banked Blood:** If not collected on the designated collection day, collect at the next available time point when biospecimens are being collected in conjunction with a participant visit.
- l. **Standard 12 Lead ECG:** ECGs will be collected at times specified in the Schedule of Activities. The Screening ECG will be a single 12lead ECG. At all other times, at each time point, 3 consecutive 12lead ECGs (triplicate) will be performed approximately 2 minutes apart to determine mean QTcF interval. All 12lead ECGs should be confirmed by a qualified individual at the institution. ECGs on Day 1 of each cycle ≥2 will be collected prior to dosing. For all participants on Cycle 1, Days 1 and 15: at predose, 1 hr and 2 hr postdose, Cycle 1, Day 8: predose, for Cycles ≥2, Day 1: predose, and at the EOT visit. When coinciding with blood sample draws for PK, the ECG assessment should preferably be performed prior to blood sample collection, such that the blood sample is collected at the nominal time. If the mean QTcF is prolonged (≥45 msec from the baseline or >500 msec), the ECGs should be reevaluated by a qualified individual at the institution for confirmation. Additional triplicate ECGs may be performed as clinically indicated.

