- m. **Standard 12 Lead ECG:** ECGs will be collected at times specified in the SoA. The Screening ECG will be a single 12-lead ECG. At all other times, at each time point, 3 consecutive 12 lead ECGs (triplicate) will be performed approximately 2 minutes apart to determine mean QTcF interval. ECG on Days 1 and 15 of cycle 1 will be collected prior to dosing. ECGs on Day 1 of each cycle ≥2 will be collected prior to dosing, and at the EOT visit. All 12 lead ECGs should be confirmed by a qualified individual at the institution. If the mean QTcF is prolonged (≥45 msec from the baseline or >500 msec), the ECGs should be reevaluated by a qualified individual at the institution for confirmation. Additional triplicate ECGs may be performed as clinically indicated. For the food effect substudy, additional ECGs should be collected at Cycle 1 Day -7: at predose, 1 hr and 2 hr postdose. After predose, a window of ±10% time is allowable.
- n. **Viral Disease Screening Tests:** HbsAg, HBcAb, anti-HBs, HCVAb, and HIV to be conducted by local laboratory where required by local regulations or if warranted by participant history.
- o. **Registration:** Participant enrollment number and dose level allocation assigned by Pfizer Inc.
- p. **For Part 2B** [REDACTED]: fulvestrant to be administered in combination with PF-07248144 (Part 2B) [REDACTED]. Detailed administration information can be found in the fulvestrant (Faslodex) USPI, and country-specific label.

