| [REDACTED]                                                                                                                                                                                       | [REDACTED]                                  |            |            |                |   | [REDACTED] |                          |   | [REDACTED] |                                                    |
| Pfizer Prep D1 banked blood k                                                                                                                                                         | X                                           |            |            |                |   |            |                          |   |            |                                                    |

**Table 4. Schedule of Activities: Pharmacokinetic Sampling, Pharmacodynamic/other Biomarker Sampling (for Parts 2A [for participants not participating in food effect substudy], 2B [REDACTED])**

| Visit Identifier        | Screening
(≤28 days
prior to
C1D1) | Cycle 1 |   |        |   |      | Cycle 2+ |   | EOT | Post-Treatment
Follow-up (28
days after EOT) |
|-------------------------|---------------------------------------------|---------|---|--------|---|------|----------|---|-----|----------------------------------------------------|
|                         |                                             | Day 1   |   | Day 15 |   |      | Day 1    |   |     |                                                    |
| Hours Before/After Dose |                                             | pre     | 0 | pre    | 0 | 4h   | pre      | 0 |     |                                                    |
| Visit Window            |                                             | -6h     |   | -30m   |   | ±24m | -30 m    |   |     |                                                    |

**\*\* NOTE:** Sample time windows apply to PF-07248144 [REDACTED] dosing only.

- a. **Part 2 (Non-food effect) PK Sampling:** Blood collections for PK sampling at predose time point (within 6 hours prior to the morning dose of PF-07248144) on Cycle 1 Day 1, predose on Cycle 1 Day 15, and for Cycles ≥2 Day 1 predose (within 30 minutes prior to the morning dose), 4 hours postdose on C1D15 (± 24 minutes); EOT and Post-Treatment Follow-Up. This PK sampling is in Part 2A, 2B [REDACTED] participants except for those participating in food effect subset.

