#### **2.2.4.1. Overview of Clinical Pharmacology for PF-07248144**

Following QD oral administration alone (at 2, 5, 8, and 15 mg) or 5 mg in combination with fulvestrant, PF-07248144 was rapidly absorbed, with a median Tmax of 3 hours based on preliminary data. Across the dose range of 2 to 15 mg, PF-07248144 steady-state AUC during the 24-hr dosing interval (AUC24 on Cycle 1 Day 15) and Cmax increased with dose in an approximately dose-proportional manner.

[REDACTED]

Please refer to the [PF-07248144 IB](#) for further information.

[REDACTED]

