##### 4.3.1. PF-07248144 Starting Dose for Monotherapy Dose Escalation

The selection of the starting dose for this FIH study is based on the preclinical toxicology results in accordance with ICH S9 Guidance entitled “Nonclinical Evaluation for Anticancer Pharmaceuticals”.

The starting dose for [REDACTED]

[REDACTED]

The predicted apparent half-life by the PBPK modeling is approximately 12 hours at the dose of 8 mg, suggesting a QD dosing regimen. For additional information, please see the Investigator Brochure (IB).

[REDACTED]

In summary, [REDACTED]

|  |  |  |  |  |  |  |  |  |  |
|--|--|--|--|--|--|--|--|--|--|
|  |  |  |  |  |  |  |  |  |  |
|  |  |  |  |  |  |  |  |  |  |

[REDACTED]

|  |  |  |  |  |  |
|--|--|--|--|--|--|
|  |  |  |  |  |  |
|  |  |  |  |  |  |
|  |  |  |  |  |  |
|  |  |  |  |  |  |
|  |  |  |  |  |  |
|  |  |  |  |  |  |

|  |  |  |  |  |  |
|--|--|--|--|--|--|
|  |  |  |  |  |  |
|  |  |  |  |  |  |
|  |  |  |  |  |  |
|  |  |  |  |  |  |
|  |  |  |  |  |  |
|  |  |  |  |  |  |

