##### Safety QTc Assessment

| Degree of Prolongation | Mild (msec) | Moderate (msec) | Severe (msec) |
|------------------------|-------------|-----------------|---------------|
| Absolute value         | >450-480    | >480-500        | >500          |
| Increase from baseline |             | 30-60           | >60           |

In addition, the number of participants with uncorrected QT values >500 msec will be summarized.

If more than 1 ECG is collected at a nominal time after dose administration (for example, triplicate ECGs), the mean of the replicate measurements will be used to represent a single observation at that time point. If any of the 3 individual ECG tracings has a QTc value >500 msec, but the mean of the triplicates is not >500 msec, the data from the participant's individual tracing will be described in a safety section of the CSR in order to place the >500 msec value in appropriate clinical context. However, values from individual tracings within triplicate measurements that are >500 msec will not be included in the categorical analysis unless the average from the triplicate measurements is also >500 msec. Changes from baseline will be defined as the change between the postdose QTc value and the average of the time-matched baseline triplicate values on Day 1, or the average of the predose triplicate values on Day 1.

In addition, an attempt will be made to explore and characterize the relationship between plasma concentration and QT interval length using a PK/PD modeling approach. If a PK/PD relationship is found, the impact of participant factors (covariates) on the relationship will be examined.

The analysis of ECG results will be based on participants in the safety analysis set with baseline and on-treatment ECG data. Baseline is defined as Cycle 1 Day 1 predose.

ECG measurements (an average of the triplicate measurements) will be used for the statistical analysis and all data presentations. Any data obtained from ECGs repeated for safety reasons after the nominal time-points will not be averaged along with the preceding triplicates. Interval measurements from repeated ECGs will be included in the outlier analysis (categorical analysis) as individual values obtained at unscheduled time points.

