#### Safety QTc Assessment

| Degree of Prolongation | Mild (msec) | Moderate (msec) | Severe (msec) |
|------------------------|-------------|-----------------|---------------|
| Absolute value         | >450-480    | >480-500        | >500          |
| Increase from baseline |             | 30-60           | >60           |

*In addition, the number of participants with uncorrected QT values >500 msec will be summarized.*

*If more than 1 ECG is collected at a nominal time after dose administration (for example, triplicate ECGs), the mean of the replicate measurements will be used to represent a single observation at that time point. If any of the 3 individual ECG tracings has a QTc value > 500 msec, but the mean of the triplicates is not > 500 msec, the data from the participant's individual tracing will be described in a safety section of the CSR in order to place the > 500-msec value in appropriate clinical context. However, values from individual tracings within triplicate measurements that are > 500 msec will not be included in the categorical analysis unless the average from the triplicate measurements is also > 500 msec. Changes from baseline will be defined as the change between the postdose QTc value and the average of the time-matched baseline triplicate values on Day -1, or the average of the predose triplicate values on Day 1.*

*In addition, an attempt will be made to explore and characterize the relationship between plasma concentration and QT interval length using a PK/PD modeling approach. If a PK/PD relationship is found, the impact of participant factors (covariates) on the relationship will be examined.*

*The analysis of ECG results will be based on participants in the safety analysis set with baseline and on-treatment ECG data. Baseline is defined as Cycle 1 Day 1 predose.*

*ECG measurements (an average of the triplicate measurements) will be used for the statistical analysis and all data presentations. Any data obtained from ECGs repeated for safety reasons after the nominal time-points will not be averaged along with the preceding triplicates. Interval measurements from repeated ECGs will be included in the outlier analysis (categorical analysis) as individual values obtained at unscheduled time points.*

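### The QTc change rule permits a Day 1 baseline recorded after the first dose, and nearly all Part 2 ECGs are taken at trough

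*Protocol*

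**What the plan says.** **Baseline.** Protocol section 9.4.5.1 defines QTc change as the difference between the post-dose value and "the average of the time-matched baseline triplicate values on Day 1, or the average of the predose triplicate values on Day 1". Later in the same section, baseline for the ECG analysis is fixed as the Cycle 1 Day 1 predose reading, with no alternative. The parallel sentence in SAP section 5.2.4 differs in the day: "average of the time-matched baseline triplicate values on Day -1".

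**Part 1 ECG times.** Table 2 footnote l: "For all participants on Cycle 1, Days 1 and 15: at predose, 1 hr and 2 hr postdose". Day 8 and later cycles are predose, and there is an end-of-treatment ECG.

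**Part 2 ECG times.** Table 3 footnote m: "ECG on Days 1 and 15 of cycle 1 will be collected prior to dosing". Day 1 of each later cycle is also predose, and there is an end-of-treatment ECG. The one exception is the food-effect subset of Part 2A, about 6 participants, who have ECGs at predose, 1 h and 2 h on Cycle 1 Day -7.

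**Exposure.** Section 2.2.4.1 gives a median Tmax "of 3 hours based on preliminary data". Table 4 footnote a has a Part 2 PK sample "4 hours postdose on C1D15", and Table 5 has the same draw for the food-effect subset. No ECG is attached to it.

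**Use of the data.** Section 9.4.5.1 tabulates each participant's largest post-dose QTc and largest increase by treatment, and plans exploratory concentration–QT modelling.

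**The concern.** Two separate things look wrong.

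First, a baseline should be free of drug. Under the protocol wording, the only Day 1 triplicates that can be time-matched to a 1 h or 2 h reading are the 1 h and 2 h readings after the first dose. Using them subtracts part of the effect that the analysis is meant to detect. Three statements in two documents now name different baselines, so two analysts could follow the text and produce different tables.

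Second, in Part 2 the readings that feed the post-dose maximum come about 24 h after the previous dose, when concentration is lowest. Part 2 is planned at about 90–120 participants, so this is the larger part of the safety data.

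**Working it through.** **1. Can each permitted baseline be computed, and is it drug-free?**

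- *Time-matched, Day 1 (protocol).* Part 1 has Day 1 triplicates at predose, 1 h and 2 h. Matching at 1 h or 2 h uses a reading taken after the first dose. On Day 1 itself the change is then the value minus itself, which is zero by construction. On Day 15 the first-dose effect is removed. For most of Part 2 there is no Day 1 post-dose reading, so the option has no separate meaning.
- *Time-matched, Day -1 (SAP).* Tables 1 to 5 show no Day -1 ECG. The screening ECG is a single tracing, and Day -7 is a dosing day for the food-effect subset only. The option cannot be computed.
- *Predose, Day 1 (both documents).* It is scheduled in triplicate, and for almost everyone it precedes any dose. In the food-effect subset it falls 168 h after the Day -7 dose. At a 12 h half-life that is 14 half-lives, and 2^(-14) = 0.00006 remains.

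Only the predose option works. No modelling is needed for this step.

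**2. Model used for size (assumption).** One compartment, oral, once daily, effect proportional to concentration. Tmax of 3 h is the reported median. The half-life comes from section 4.3.1: "The predicted apparent half-life by the PBPK modeling is approximately 12 hours at the dose of 8 mg". It is a prediction, so 6 h and 24 h are shown as an assumed range. Up to a factor that cancels in ratios:

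- single dose: D(t) = e^(-ke·t) - e^(-ka·t)
- steady state: S(t) = e^(-ke·t)/(1 - e^(-24ke)) - e^(-ka·t)/(1 - e^(-24ka))

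For a 12 h half-life, ke = ln2/12 = 0.0578, and ka = 0.863 places the steady-state peak at 3 h. Then:

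- S(3) = 0.8409/0.75 - 0.0751 = 1.046
- S(24) = 0.25/0.75 = 0.333
- S(2) = 0.8909/0.75 - 0.1780 = 1.010
- S(4) = 0.7937/0.75 - 0.0317 = 1.027
- D(2) = 0.8909 - 0.1780 = 0.713

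| Half-life | Trough/peak S(24)/S(3) | 2 h/peak S(2)/S(3) | 4 h/peak S(4)/S(3) | First dose/steady state at 2 h D(2)/S(2) |
|---|---|---|---|---|
| 6 h (ka 0.690) | 0.11 | 0.95 | 0.97 | 0.91 |
| 12 h (ka 0.863) | 0.32 | 0.965 | 0.98 | 0.71 |
| 24 h (ka 0.969) | 0.56 | 0.98 | 0.99 | 0.46 |

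A hand check of the trough with simple decline from 3 h to 24 h: 2^(-21/12) = 0.30.

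**3. Baseline limb.** The last column is the share of the Day 15, 2 h effect that a time-matched Day 1 baseline would subtract: about 71% (46–91%).

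**4. Part 2 limb.** Predose readings sit at about 32% of peak (11–56%). An assumed 15 msec effect at peak would appear as 15 × 0.32 = 4.8 msec (15 × 0.11 = 1.7 to 15 × 0.56 = 8.4). A 4 h reading would sit at 97–99% of peak.

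**5. Part 1 limb.** With Tmax 3 h, the 2 h concentration is 94–98% of peak (single dose and steady state together). With an individual Tmax of 4 h it is 84–94%. Sections 2.2.4 and 2.2.4.1 report 7 participants at 8 mg and 6 at 15 mg, an expansion dose of 5 mg, and roughly dose-proportional exposure. At 96% of peak, a 2 h ECG at 15 mg is at about 0.96 × 15/5 = 2.9 times the peak at 5 mg, and at 8 mg about 0.96 × 8/5 = 1.5 times.

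**The case against.** The strongest reply on baseline is that the protocol simply lost a minus sign. The SAP sentence is nearly identical and reads Day -1, and the same protocol section states a predose baseline, so no post-dose baseline may have been intended. That is plausible, and nothing shows that such a baseline will be used. It does not rescue the rule, because no ECG is scheduled on Day -1. On either reading the option is unusable or biased.

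On timing, three stronger inferences are tempting, and the documents do not support them.

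- *That QTc testing is blind to peak exposure.* In Part 1 the 2 h reading is close to peak when Tmax is 3 h, and only moderately lower for a later absorber.
- *That the concentration–QT model lacks data near peak.* It needs a range of concentrations, and Part 1 supplies paired ECG and PK points above the expansion-dose peak.
- *That every Part 2 dosing-day ECG is predose.* The Day -7 ECGs in the food-effect subset are not.

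It is also fair to say that QTc is not a listed primary or secondary endpoint, that the modelling is exploratory, that extra triplicates are allowed when clinically indicated, and that Part 2A had already treated 33 participants at the September 2022 cutoff. These points lower the stakes and limit how many participants a timing change can reach. Reactive ECGs do not give systematic coverage near peak, and Part 2B had treated only 8 of about 30.

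**Conclusion.** The baseline wording is wrong as it stands. Section 9.4.5.1 permits a baseline that conflicts with its own definition and, in Part 1, can only be taken after dosing. The SAP's version refers to an ECG that the schedules do not contain. This conclusion rests on the documents alone. Only its size, about 71% (46–91%) of the Day 15 effect at 2 h, depends on the model.

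The Part 2 timing is an improvement worth making rather than an error. Apart from about 6 participants on one day, the dosing-day readings behind the Part 2 maximum are troughs, at roughly 32% of peak (11–56%). The range is wide because the half-life is predicted rather than observed, and a delayed QT effect would change the picture.

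The Part 1 gap between 2 h and the 3 h median Tmax is real but minor and optional to address.

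**What to change.** **Baseline.** In protocol section 9.4.5.1 and SAP section 5.2.4, delete the time-matched option and keep the Cycle 1 Day 1 predose triplicate mean as the only baseline. This costs nothing and needs no new data.

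**Part 2, participants still to be enrolled.** Pair the Cycle 1 Day 15 triplicate with the existing 4 h PK draw in Tables 4 and 5. This adds no ECG and no visit. The Day 15 predose ECG is given up, while the predose ECGs in later cycles remain. If the clinical team needs the Day 15 predose reading for monitoring, the alternative is one extra triplicate per participant. For combination cohorts, check first that 4 h also suits the partner drug, whose details are redacted here. For participants already treated, label the Part 2 table as based on predose readings.

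**Part 1.** Optional: in cohorts still open, move the 2 h triplicate to the existing 3 h PK draw. The 2 h reading would be lost.

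None of this bears on the QTc thresholds for holding or stopping treatment, which are a clinical matter.

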## DOSE EXPANSION (Part 2)

**Table 3. Schedule of Activities: Dose Expansion (Part 2)**

| Visit Identifier                                               | Screening
(≤28 days
prior to
Cycle 1,
Day 1) a | Cycle 1
(28 days) |        | Cycle 2
(28 days) |        | Cycles 3+,
(every 28 days) |        | (EOT) b | Post-
Treatment
Follow-up
(28 days
after EOT) c | Long-
Term
Follow-
up |
|----------------------------------------------------------------|-----------------------------------------------------------------------|----------------------|--------|----------------------|--------|-------------------------------|--------|--------------------|------------------------------------------------------------------------|--------------------------------|
|                                                                |                                                                       | Day 1                | Day 15 | Day 1                | Day 15 | Day 1                         | Day 15 |                    |                                                                        |                                |
| Visit Window                                            |                                                                       | ±2D                  | ±2D    | ±2D                  | ±2D    | ±2D                           | ±2D    | ±7D                | +7D                                                                    |                                |
| Informed consent d                                  | X                                                                     |                      |        |                      |        |                               |        |                    |                                                                        |                                |
| Medical/Oncological
history e                    | X                                                                     |                      |        |                      |        |                               |        |                    |                                                                        |                                |
| Full Physical examination f                         | X                                                                     |                      |        |                      |        |                               |        | X                  |                                                                        |                                |
| Brief physical examination f                        |                                                                       | X                    | X      | X                    | X      | X                             | X      |                    | X                                                                      |                                |
| Height                                                         | X                                                                     |                      |        |                      |        |                               |        |                    |                                                                        |                                |
| Weight                                                         | X                                                                     | X                    |        | X                    |        | X                             |        | X                  | X                                                                      |                                |
| Vital signs g                                       | X                                                                     | X                    | X      | X                    | X      | X                             | X      | X                  | X                                                                      |                                |
| ECOG Performance status h                           | X                                                                     | X                    |        | X                    |        | X                             |        | X                  | X                                                                      |                                |
| Contraception check i                               | X                                                                     | X                    |        | X                    |        | X                             |        | X                  |                                                                        |                                |
| Concomitant medication(s) j                         | X                                                                     | X                    | X      | X                    | X      | X                             | X      | X                  | X                                                                      |                                |
| Laboratory                                              |                                                                       |                      |        |                      |        |                               |        |                    |                                                                        |                                |
| Hematology k                                        | X                                                                     | X                    | X      | X                    | X      | X                             | X      | X                  | X                                                                      |                                |
| Blood chemistry k                                   | X                                                                     | X                    | X      | X                    | X      | X                             | X      | X                  | X                                                                      |                                |
| Coagulation k                                       | X                                                                     | X                    |        |                      |        | X (every
8 weeks)          |        | X                  |                                                                        |                                |
| Urinalysis k                                        | X                                                                     |                      |        |                      |        |                               |        | X                  |                                                                        |                                |
| Pregnancy test l                                    | X                                                                     | X                    |        | X                    |        | X                             |        | X                  |                                                                        |                                |
| (Standard 12-lead) ECG m                            | X                                                                     | X                    | X      | X                    |        | X                             |        | X                  |                                                                        |                                |
| Viral disease screen
(Hepatitis B, C, and HIV) n | X                                                                     |                      |        |                      |        |                               |        |                    |                                                                        |                                |
| Registration and
treatment                          |                                                                       |                      |        |                      |        |                               |        |                    |                                                                        |                                |
| Registration o                                      | X                                                                     |                      |        |                      |        |                               |        |                    |                                                                        |                                |

